### Trial status

The trial is expected to start recruiting the first participants in August 2017. Follow-up assessments, including data analysis, are expected to be completed by December 2019.

## Discussion

The objective of this study is to develop an individually targeted manual-based VR program for patients with an ABI and evaluate its effectiveness measured as hours in employment/study and costs when compared to conventional VR provided by the municipalities.

To our knowledge, this is one of the first studies to take a holistic approach and formalize the collaboration between municipalities, a specialized rehabilitation team, and family caregivers in order to improve VR for patients with ABI. The results of this study will provide several innovative contributions to the existing literature regarding the feasibility and effectiveness of this VR intervention important for the allocation of resources in future VR programs.

An important element in this VR program is the individualized approach, aiming to support the participant in the work/everyday life balance, cognitive, and functional problems as well as providing individual support for gaining and sustaining employment. In Denmark, the municipalities have the responsibility to offer rehabilitation and therefore an important issue in this study is to focus on the cooperation with the municipalities. The different elements of this VR program will be described in separate manual-based procedures increasing the knowledge of the different “ingredients” used to the different participants. Thus, the positive effect of this program should provide measurable progress in employment status and participation, level of fatigue, functional disability, and HRQoL. However, the study will not be able to determine which element or elements in the VR program are the most effective or if some could be omitted or increased in intensity. Instead, this study will provide knowledge about how the VR intervention differentiates from the program in the municipality, since the elements (modules) are described and the effect and utility costs are evaluated.

The study gains its strength from the participation of various municipalities spread across the Zealand Region and the Capital Region of Denmark that will ensure that different types of ABI will be represented in the study. An additional strength is the inclusion of family caregivers in the VR intervention, which facilitate that the effects will be implemented and anchored after the VR intervention ended that could otherwise be lost. Furthermore, the family intervention program addresses the family function as a whole, which more or less is an overlooked issue in Danish rehabilitation.

The study is limited by a number of factors. First, the study will not include patients that for some reasons are unwilling to participate in the study but fulfill the inclusion criteria. However, when possible, the reason for refusal and some baseline questions will be obtained and included in the analysis in order to avoid recruitment biases. Second, both the participants and the rehabilitation team will not be blinded to the allocation, but the cluster randomization and blinding of the researchers should ensure that contamination does not occur. Third, the control intervention may most likely vary across the municipalities that participate in the study and may also vary nationwide, affecting the social benefits and vocational terms.

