**Methods:**

This study is an interventional, two-arm, six-month follow-up, cluster randomized controlled trial involving four municipalities in the Zealand Region and the Capital Region of Denmark. A total of 84 patients with ABI evenly distributed across four municipalities will be included in the study. The patients will randomly be allocated in a 1:1 ratio to the VR intervention provided by a specialized Brain Injury Centre or the conventional VR provided by the municipalities (usual care). The six- to nine-month intervention will consist of individual and group therapies as well as a work placement program including supported employment. Furthermore, the intervention will include a family intervention program followed up by support to one individual family caregiver. The primary outcomes are increased work or study rate at six-month follow-up. Moreover, a budget impact analysis and possibly a cost-utility analysis of the intervention will be performed.

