## Methods/Design

### Trial design and hypotheses

An interventional, two-arm, six-month follow-up, cluster RCT (Fig. 1) including 84 participants with an ABI allocated randomly (allocation ratio 1:1) to the VR intervention and control group that consists of a conventional VR program (usual care).

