### Randomization

To avoid confounding between the VR intervention and the control group due to random probability, the number of cases and controls within each of the enrolled municipalities is set to be the same (+1/–1). Due to the prospective nature of the inclusion, which practically means that the number of patients included within each municipality is not known a priori, the randomization is performed by randomly assigning the first patient within each municipality to either the VR intervention or the conventional VR program. The following patient (within each municipality) is then assigned consecutive to the other group and so forth. This randomization scheme ensures equal distribution of cases and controls, both within each municipality as well as in time, avoiding confusion of these two factors. Controlling the distribution over time is central in such a study where some variation over the trial period due to protocol familiarity of the rehabilitation team at the Brain Injury Centre may be expected.

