### Statistical analysis

Data analysis will be conducted using the statistical program R version 3.2.2. Baseline characteristics of the participants will be reported to ensure homogeneity between the VR intervention and the control group (reported as mean and standard deviation for continuous variables and proportions for categorical variables). Differences between baseline characteristics for continuous variables will be tested by an independent samples *t*-test or a Mann–Whitney U test dependent on the distribution of the data. Categorical variables will be analyzed by a Chi-square test. If any significant differences between the VR intervention and the control group are found, these will be adjusted for in the downstream analyses.

The differences between the VR intervention and the control group for the primary and secondary outcomes will be analyzed using repeated measurements statistical tools and multilevel analysis, including possible confounders (e.g. age, gender, ABI severity, socioeconomic status pre-injury, education, or recruitment site). *P* values and 95% confidence intervals will be provided and *P* < 0.05 will be considered statistical significant.

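### The trial is labelled cluster randomised and relies on that to exclude contamination, but patients are allocated individually within each municipality, so clustering gives no such protection

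*Protocol article*

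**What the plan says.** The Abstract (Methods) describes a "cluster randomized controlled trial involving four municipalities", and the section Trial design and hypotheses opens with "An interventional, two-arm, six-month follow-up, cluster RCT (Fig. 1) including 84 participants". The limitations paragraph of the Discussion concedes that participants and the rehabilitation team are unblinded, then states that "the cluster randomization and blinding of the researchers should ensure that contamination does not occur".

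The passages on allocation name the patient as the unit:

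- Abstract (Methods): "The patients will randomly be allocated in a 1:1 ratio to the VR intervention".
- Trial design and hypotheses: the participants are "allocated randomly (allocation ratio 1:1) to the VR intervention and control group".
- Randomization: the scheme works by "randomly assigning the first patient within each municipality to either the VR intervention or the conventional VR program". Each later patient in that municipality goes to the arm opposite to the previous one, and arm sizes within a municipality may differ by at most one.
- Description of the interventions: participants are assigned after individual consent and completion of the baseline questionnaires.

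Sample size and power counts 42 + 42 individuals, with no intracluster correlation or design effect. Statistical analysis mentions multilevel analysis without naming the levels. Municipality enters only at the end of a list of examples of possible confounders, as "or recruitment site".

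**The concern.** Cluster randomisation limits contamination because whole units receive one arm, so staff and patients in a unit do not meet the other arm. If each unit contains both arms, that mechanism is absent. The protocol names it as one of two reasons why contamination should not occur. The other, blinding of researchers, concerns how outcomes are recorded and analysed. It cannot stop ideas, methods or expectations reaching control patients or those who serve them.

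Interpretation is what is at stake. If the programme works and some of its content reaches controls, the contrast shrinks toward zero. A reader who accepts the Discussion's statement would take a small or null difference as free of such dilution. A secondary issue is that the factor on which allocation is deliberately balanced is not firmly in the analysis, although the Discussion itself expects control care to vary across municipalities.

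**Working it through.** **1. What is the unit of allocation?**

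| Section | What it implies |
|---|---|
| Abstract, Methods (design label) | Cluster |
| Trial design and hypotheses (label) | Cluster |
| Discussion, limitations | Cluster |
| Abstract, Methods (allocation sentence) | Patient |
| Trial design and hypotheses (allocation phrase) | Patient |
| Randomization | Patient, alternating within municipality from a random start |
| Description of the interventions | Participant, after consent and baseline questionnaires |
| Sample size and power | 42 + 42 individuals, no cluster term |

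No section describes randomising a municipality or any other group. With 84 patients spread evenly over four municipalities, each has 84/4 = 21 patients. The within-one rule then puts 10 in one arm and 11 in the other in every municipality. Municipality is a stratum.

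**2. What separates the arms?** The Brain Injury Centre team delivers the intervention and the municipality delivers usual care. Intervention patients do not receive municipal usual care (Patient recruitment and eligibility). Participants and the team are asked not to disclose allocation or content (Blinding). Against this, the same municipal case managers refer patients to the study and complete questionnaires on each participant. The unblinded rehabilitation team also interviews control patients to evaluate the conventional programme (section on conventional VR). None of the separation comes from clustering.

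**3. The plan's power figure.** Inputs from Sample size and power: means 10 and 14 hours, overdispersion 4 (variance = 4 × mean), 42 per arm, alpha 0.05.

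- SE = √[4 × (10 + 14)/42] = √2.286 = 1.512
- z = 4/1.512 = 2.646
- Two-sided power = Φ(2.646 − 1.960) = 0.754

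The plan states 0.8. A one-sided test gives 0.84. The stated value is a one-decimal example read from a colour chart, and the gap is a separate matter. The value 0.754 is used below only so that the comparisons share one basis.

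**4. Illustration of dilution.** Assume a share c of controls obtains the full 4-hour gain. The control mean becomes 10 + 4c, the difference 4(1 − c), and SE = √[4 × (24 + 4c)/42].

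| Assumed c | Difference (h) | SE | z | Two-sided power |
|---|---|---|---|---|
| 0 | 4.0 | 1.512 | 2.65 | 0.75 |
| 10% | 3.6 | 1.524 | 2.36 | 0.66 |
| 20% | 3.2 | 1.537 | 2.08 | 0.55 |

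The values of c are assumptions. The documents give none.

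**The case against.** The best reply is that little depends on the label. The procedure, the sample size and the analysis all treat patients as the units. The arms have different providers, and the intervention is a programme of 6 to 9 months run to the centre's own operating procedures. Referring patients and filling in questionnaires does not transmit such a programme. A municipality that finds a workplace for an intervention patient is helping that arm, not passing intervention content to controls. Dilution would also work against the intervention, so it would not produce a false positive. All of this stands, and it limits the point. It does not rescue the Discussion's sentence, which attributes the absence of contamination to two features that cannot deliver it.

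Three stronger readings are tempting, and the documents do not support them.

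- A reader might infer that the trial is badly underpowered because the sample size omits a design effect. That would apply if municipalities were randomised; they are not, so no such inflation is due.
- A reader might infer that the analysis uses the wrong error structure. Nothing in Statistical analysis treats municipality as the randomised unit, and a multilevel model with site can suit a multisite trial. Its detailed form may properly be left to an analysis plan.
- A reader might infer that substantial contamination will occur. The documents show that it is possible, but give no rate.

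Nor would calling the trial simply individually randomised be accurate. Only the first patient in each municipality is randomised and the rest alternate. The predictability of that sequence is a separate issue.

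**Conclusion.** The point holds as a misdescribed design and an unsupported claim about bias. The cluster label in the Abstract, in Trial design and in the Discussion contradicts the allocation procedure, and the protection from contamination drawn from it does not exist. Researcher blinding does not replace it. What remains is separation by provider and by a request not to disclose, which may be adequate but is not guaranteed.

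The size of any dilution is unknown. Under the assumed full-effect contamination of 10% or 20%, power falls from about 0.75 to about 0.66 or 0.55. These figures show sensitivity and are not estimates. The direction, toward no effect, assumes that the programme is beneficial.

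This should be fixed. It does not alter the sample size or the comparison being made, but it changes what a null or small difference can be taken to mean.

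**What to change.** 1. In the Abstract, Trial design and hypotheses, and the Discussion, replace the cluster label with individual allocation within municipality, with municipality as stratum. Describe the method as alternation from a random start, unless the allocation method is itself changed.
2. Delete the statement that cluster randomisation and researcher blinding ensure no contamination. Say instead that separation rests on different providers and the non-disclosure request, that contamination within municipalities remains possible, and that it would bias toward no effect.
3. Report what control patients received, using the patient interviews already planned in the section on conventional VR and the service-use data planned under Economic evaluation.
4. Include municipality in the primary and secondary models as the stratification factor, for example as a fixed effect, and not as an optional confounder.
5. If power under contamination is shown, label the rates as assumptions.

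The cost is wording, some reporting from sources already planned, and 3 degrees of freedom if there are four sites. The Abstract says four; Patient recruitment and eligibility says only that there are several.

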## Abbreviations

ABI: Acquired brain injury
CBS: Caregiver Burden Scale
DMFS: Dutch Multifactor Fatigue Scale
EQ-5D-3L: EuroQol five dimensions questionnaire
FACES-IV: Family Adaptability and Cohesion Scale
GOSE: Glasgow Outcome Scale Extended
HADS: Hospital Anxiety and Depression Scale
HRQoL: Health-related quality of life
MPAI-4: The Mayo-Portland Adaptability Inventory
PSI: Problem Solving Inventory
QALY: Quality adjusted life-years
SF-12: 12-Item Short Form Health survey
SOP: Standardized operating procedure
SPB: Self-Perceived Burden Scale
TUG: Timed Up and Go
VR: Vocational rehabilitation
